We also considered the nature of a comparison intervention in the control arm. The most common response towards a person with weight problems in primary care is not to discuss this [22,24]. A reasonable comparator would therefore be no intervention. On the other hand, asking a person to participate in a trial related to weight management and offering no intervention makes it clear that a person is in the control arm. This could lead to differential follow-up, which would threaten validity. In the Lighten Up trial, people were more likely to agree to follow-up weighing when a person had lost weight than when they had not. The second most common response GPs make is to advise that weight loss would benefit health - an advice-orientated intervention [22,24]. We believe that offering advice to lose weight on health grounds to the control group does not reveal the random allocation to the participant and may assist follow-up. The Lighten Up trial showed that CWMS achieve higher weight loss than participants who try to lose weight unassisted and therefore there is a reasonable prospect of detecting a difference in effect between our advice-orientated control intervention and our assistance-orientated active intervention.

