The third purpose is to measure participants’ reactions to the GP discussing weight management, immediately after their GP appointment, when they visited for reasons other than their weight (Outcome #5). The research assistant (RA) will ask all participants, upon exit of their appointments, for their randomization card and envelope (and withdrawal card if applicable). The randomization card will ask participants to rate the helpfulness and the appropriateness of the GPs very brief intervention on five-item Likert-type scales that the GP and/or RA will ask the participant to complete; this will be carried out confidentially in the RAs room. Where patients have not been randomized, the RA would explain that the GP does not feel it is suitable for them to be involved in the trial at this time and, therefore, they have not been enrolled; GPs will be asked to record why the patient was not randomized (see below).

##### 

**Follow-up telephone call at 3 months (after enrolment)** A researcher will contact all participants via telephone (or by alternative methods such as email, post or text message if telephone contact is not possible) 3 months after their initial appointment to assess what actions they have taken, if any, to manage their weight since the appointment (Outcome #6). We will also assess if participants are continuing to manage their weight and through which methods. If they are no longer managing their weight, we will ask why and record this on a simple checklist of possible reasons. We will ask participants to stand on their scales and read out their weight or report a recently obtained weight (Outcome #2). We will also ask how many contacts participants have had with their GP where the prime purpose was weight management. Pregnancy status will also be updated to ensure weight data are valid.

##### 

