#### Randomization of participants

Participants will be randomized to a treatment arm at the baseline visit, which will be conducted at their own GP practice (see Measurement of outcomes [Visit 1, Baseline] for details). The RA will give eligible patients who are willing to participate in the trial an opaque A4 sealed envelope, which will contain a color-coded randomization card. The envelopes will be numbered in sequence. We will use block randomization of randomly sequenced blocks of 2 and 4 stratified by GPs, which will balance individual consulting styles. The trial statistician will be responsible for the production of randomization schedule, prior to recruitment.

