The RA will ask patients to give the sealed envelope to their GP upon entering their consultation. The card inside the sealed envelope will reveal to the GP, but not the patient, which intervention to deliver. We will ask GPs not to open the randomization envelope until they are satisfied that it is suitable for the patient to be included in the trial (that is, after they have addressed the patient’s primary reason for visiting them and feel that it would be clinically appropriate to offer a brief intervention at this time to this patient - see Exclusion criteria above; once the randomization envelope is opened then the patient has been enrolled in the trial. It would undermine the ability of the study to detect differences between the arms if we enrolled participants who did not receive an intervention. Attached to the outside of each randomization card envelope will be a detachable ‘patient withdrawal card’. The RA will discretely write the patient’s weight and BMI on the back of the withdrawal card before handing the sealed envelope to them so that the GP will be aware of their up-to-date measurements, if required, during the consultation. Furthermore, there will be a tick box option on the card for GPs to select if they did not randomize the patient in to the trial, indicating that the person has not been randomized and therefore not enrolled. The tick box will indicate the reason for non-enrolment (that is, clinically inappropriate, not appropriate in the consultation or special reasons). If ‘special reasons’ is selected, the GPs will be asked to state why, if they can without breaking patient confidentiality, in the space provided. The sealed envelope and withdrawal card would be returned to the RA by the patient after their consultation (see Measurement of outcomes [Visit 1, Baseline]) and the envelope will then be replaced at the top of the randomization envelope pile for use by the next appropriate potential participant.

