#### Unblinding

Due to the nature of this trial, it is necessary for the GPs and RAs to be aware of the patient’s treatment group allocation to ensure the correct intervention is provided. Thus, these personnel cannot be blinded to treatment. Patients and the members of the research team that will conduct follow-up assessments, however, will be blinded to treatment allocation.

As this is an open label trial the issue of unblinding the clinicians caring for the patient does not arise.

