To examine the fidelity of the interventions, we will seek the permission of both participants and GPs to audio-record the brief intervention component of a proportion of consultations (n = 5) by each GP. Most GPs will be familiar with recording their consultations as part of their training and most patients agree to this. To examine for evidence of consultation distortion, we will take the first 30 participants who have been recorded and compare the immediate post-consultation ratings of helpfulness and appropriateness to those not recorded. If evidence of distortion is found, we will not continue the recordings. Fidelity in the intervention group will be assessed by recording whether or not an offer of referral was made and whether or not there was supporting discussion (for example, encouragement to attend, advice on the superiority of the service over trying alone). Fidelity in the control group will be assessed on whether advice was given that linked weight loss to improved health and that no offer of referral to weight management was made.

Participants in the assistance-orientated intervention (that is, practical support) group will be offered referral to an evidence-based CWMS available in the NHS; for example, SW or RC. Immediately after the GP appointment, RAs at the GP practice will provide the intervention group participants with their weight management referral packs and assist booking the participant’s first appointment. Group leaders of these CWMS undertake rigorous weight management training through their organization and are expected to follow standard procedures.

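### Outcome 5 is rated on the allocation card, possibly at the rated GP's request, with no order set against the support-arm referral pack, so the between-arm comparison is at avoidable risk of bias

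*Protocol article*

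**What the plan says.** Four parts of the protocol article bear on this.

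- **Measurements of outcomes, Visit 1.** Outcome 5 is the participant's reaction to the GP raising weight, taken straight after the consultation. The instrument is the randomization card: "The randomization card will ask participants to rate the helpfulness and the appropriateness of the GPs very brief intervention on" Likert-type scales. These are scales "that the GP and/or RA will ask the participant to complete; this will be carried out confidentially in the RAs room". The RA "will ask all participants, upon exit of their appointments, for their randomization card and envelope".
- **Randomization of participants.** The patient carries in "an opaque A4 sealed envelope, which will contain a color-coded randomization card". On what it discloses: "The card inside the sealed envelope will reveal to the GP, but not the patient, which intervention to deliver".
- **Unblinding.** GPs and RAs know the allocation. "Patients and the members of the research team that will conduct follow-up assessments, however, will be blinded to treatment allocation".
- **Interventions and Treatment providers.** In the support arm the RA is to book a local group at once where possible. "Immediately after the GP appointment, RAs at the GP practice will provide the intervention group participants with their weight management referral packs", and the RA helps arrange the first session. The control arm has no counterpart to this step.

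The ratings have at least two uses. The statistical methods compare the two-item total between arms by t-test or Mann–Whitney test, and each item by Mann–Whitney test. Treatment providers uses the same ratings to compare the first 30 recorded participants with unrecorded ones, and recording stops if distortion is found.

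**The concern.** Secondary objective 3 asks how patients feel about the GP raising weight and whether that varies by type of intervention. For the arm contrast to answer this, the rating should be taken in the same way in both arms and should reflect the consultation alone. Three features of the stated procedure work against that.

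1. The rating form is also the allocation document. The patient has to read and mark a card whose other purpose is to tell the GP the arm.
2. The person being rated may request the rating. The wording also lets the requester differ from one participant to the next, and both possible requesters know the allocation.
3. One arm receives a tangible service from the RA in the same period in which that RA role collects the rating. The article does not say that the rating comes first.

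At stake is whether a difference in Outcome 5 can be read as a difference in reaction to what the GP said. The recording check inherits the problem. If the requester, or the order of rating and pack, differs between recorded and unrecorded consultations, the check mixes that difference with any effect of recording.

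**Working it through.** The protocol states no figure on this point. Its sample size concerns weight change and is not in question. The check is a reading of the sections against each other.

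**Step 1: is the rating form the allocation card?** Yes. Measurements of outcomes names the randomization card as the place where the scales are printed. Randomization of participants describes one color-coded card in the envelope and says it tells the GP what to deliver. No separate rating form is described for this step.

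**Step 2: does the patient handle it?** Yes. The RA asks the participant for card and envelope on leaving the consultation, and the participant completes the scales in the RA's room.

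**Step 3: does this contradict patient blinding?** Not outright. The article says the card does not disclose the arm to the patient and does not reproduce its wording. A color whose meaning only the GP knows could be handled without learning the arm. But one object is asked both to inform the GP and to be read and marked by a patient who is to stay uninformed. Whether that works depends on card content that the article does not show. This is a tension to reconcile, not a demonstrated breach.

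**Step 4: who asks for the rating?** Either the GP or the RA, or both. Completing it in the RA's room protects the answer from being seen by the GP. It does not remove the influence of having been asked by the GP, and it does not make the requester the same for everyone.

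**Step 5: what happens around the rating in each arm?**

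| Step after the consultation | Support arm | Control arm |
|---|---|---|
| RA takes back card and envelope | Yes, on exit | Yes, on exit |
| Rating completed in RA's room | Yes | Yes |
| RA provides referral pack and booking help | Yes, straight after the appointment | No |
| Order of rating and pack | Not stated | Not applicable |

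Both the rating and the pack are placed directly after the appointment and assigned to the RA role. That they fall in one contact is a fair inference but is not stated, and the article allows booking by a later telephone call. If the rating always comes first, the pack cannot influence it. If it sometimes comes second, the influence falls on one arm only.

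**Step 6: is the pack simply part of what is being rated?** Only in part. Outcome 5 and the card both concern the GP's discussion. Under the assistance-orientated treatment, the article says that outside the trial the GP would refer as for any other service, and that the research team does it here on advice. The RA's help is therefore a trial arrangement, separate from the GP's words.

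**Step 7: can a size be given?** No. The article gives no standard deviation and no expected difference for Outcome 5, and nothing on how many participants would rate after receiving the pack or at the GP's request.

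**The case against.** The strongest reply has five parts.

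- **The card need not unmask anyone.** The article says it does not reveal the arm to the patient, and by the time of rating the patient has already heard either an offer of referral or health advice. This stands. A reader might infer that patient masking is broken, but the documents support only a risk.
- **The primary outcome is not touched.** A reader might connect the card with the Background's warning, "This could lead to differential follow-up, which would threaten validity". That warning is about a no-intervention control, which would make it obvious to participants that they were controls. It is not about a rating card. Weight at 12 months is to be measured objectively, and follow-up assessors are stated to be blinded. This stands, and no claim about follow-up or the primary outcome is made here.
- **A GP request can occur in either arm.** True, so it gives no bias in a known direction. But the GP knows the allocation and the requester is left open, so equality between arms is not assured.
- **The order of RA steps is detail that a journal article leaves out.** Partly fair. The full working procedure may put the rating first, and both steps are described as immediate. But the article does fix the instrument and the possible requesters, and those two choices are open to criticism as stated.
- **Liking a free referral is a proper reaction to the offer.** Agreed. Only the added effect of receiving the pack and booking help from the RA is extraneous.

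A reader might also try to size the bias by applying the 30% take-up from the sample size section to an assumed rise in rating. The documents do not support this. That figure is an assumption about taking up referral in the weight-loss calculation. It does not count people who hold a pack when they rate, and no rise in rating has any basis in the article.

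**Conclusion.** The point holds as an avoidable risk of bias in the between-arm comparison of Outcome 5, and in the recording check that relies on the same ratings. It rests on two stated choices (rating on the allocation card, and the rated GP as a permitted requester) and on one unset order (rating against a pack given in one arm only). The third element assumes that rating and pack can fall in the same contact, which the text suggests but does not say.

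Neither the size nor the direction of any net bias can be established from the article. Outcome 5 is a non-efficacy outcome, which limits the consequence, but it answers a stated secondary objective and is formally tested between arms. The remedy is cheap enough to be worth making on that basis.

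**What to change.** 1. Print the two rating items on a separate plain slip that carries only the study number, with no arm color or code.
2. Have the RA, not the GP, give the slip to every participant in both arms in the RA's room, as the first step after the consultation and before any referral pack or booking.
3. In the Visit 1 text, remove the GP as a possible requester of the rating.
4. Reconcile the Visit 1 text with Randomization of participants and Unblinding, so that it is clear who sees the randomization card and how the patient is kept from learning the arm.

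The cost is one extra printed slip per participant and a fixed order of steps for the RA, with no added staff or visits. Recruitment began in June 2013, so the change can apply only to participants still to be enrolled. The Discussion shows that field procedures have already been adjusted during the trial. The date of the change should be recorded so that ratings taken before and after it can be told apart.

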#### Loss to follow-up

We will make a maximum of three attempts to contact participants before abandonment, using multiple means and trying different times. More than this could be seen as harassment. If participant’s data is missing we will use ITT analysis with BOCF for the primary outcome assessment (see below – Description of Statistical Methods).

### Study participants

#### Overall description of study participants

In total, 1,824 obese adults in England attending their GP for reasons other than weight management; 912 in each of the two treatment groups (see Sample size calculations below).

#### Inclusion criteria

Any patient, during recruitment, that:

• Is identified with a body mass index (BMI) ≥30 (or ≥25 for South Asian population groups) and excess body fat.

• Is ≥18 years of age.

• Consents to participate and comply with study procedures.

#### Exclusion criteria

The participant may not enter the study if any of the following apply:

• Pregnant or intending to become pregnant during the trial period (that is, the next 12 months).

• Currently or within the past 3 months participated in a weight management program (including pharmacotherapy or bariatric surgery).

• Unable to understand and speak English sufficiently to give informed consent and complete the research assessments.

• Visiting the GP for weight management.

• The GP deems it inappropriate to make an opportunistic intervention on weight management. This includes personal medical reasons known to the GP, such as an eating disorder, or reasons related to the consultation (for example, the patient has become distressed and it would seem insensitive to make such an intervention at that time). If the GP does not consider it appropriate, then the patient will not be enrolled and randomized into the trial (see Randomization of participants below).

### Study procedures

#### Informed consent

The Recruitment of participants section below specifies who will take informed consent and how and when it will be taken.

#### Study assessments

The Measurement of outcomes section above outlines the different stages of the study, including each assessment and time points. The sections below outline additional study procedures (that is the recruitment of GP practices and participants and the randomization, enrolment and withdrawal procedures).

#### Recruitment of GP practices

We will invite practices to participate without restriction as to the type of practice.

#### Recruitment of participants (including screening, eligibility and baseline assessment)

The trial will involve about 60 GP practices within England, where we propose recruiting our participants. On arrival at the practice, the receptionist will provide a participant information leaflet (PIL) to each patient attending for a GP consultation during that recruitment session. The PIL would inform patients that everyone visiting a GP during that session will be asked, by a RA before their appointment with the GP, if they (that is the RA) could briefly take a few measurements to update the practice medical records (as identified in Visit 1 - Baseline, Form 1, above). The PIL will also state “This is part of a study that is taking place at the practice; the researcher will tell you more. The researcher will also ask for your name, date of birth, ethnicity, and the language you speak. This will be done in a private consultation room and take less than 10 minutes. If you do not want to see the researcher, you do not have to. It will not affect the care we give you in practice today or in the future”. In practices where patients check-in for their appointment via an automated computer system upon arrival, rather than seeing a receptionist, the PILs will be positioned by the check-in system, and the on-screen message will be programmed to ask the patient to take one.

To check the patient’s health, the RA will measure height and weight and percentage body fat of willing patients in a vacant consultation room using medically approved and validated weighing scales (Tanita portable body composition analyser, model SC 240 MA); the RA will ask participants to remove excess clothing (for example, coats and large jumpers) and shoes to increase accuracy of body weight, body fat and height. On the advice of our GP consumer group, we will ask receptionists booking patients for this session to advise patients that this health check will be taking place and ask them to attend about 10 minutes prior to the appointment if possible. This is designed to help prevent disruption to the GP appointment schedule and provide reassurance to the patient that they have time to speak with the RA and will not miss or delay their appointment.

During the height, weight and body fat assessment, the RA will collect socio-demographic data (see Measurement of outcomes [Visit 1, Baseline] for details), so that the research team can examine whether the population enrolled were a biased selection of all those attending and, as a secondary benefit, to update the GP records. The RA will invite patients meeting the trial eligibility criteria (see Inclusion and Exclusion criteria above) to participate “in a study about people’s reactions and response to GPs discussion of their weight”; the RA will explain the trial to interested patients and answer any questions that they may have, as well as provide them with a trial patient information sheet (PIS) for future reference. If the patient is willing to participate, the RA will seek immediate written informed consent to participate in the trial (that is, trial consent) prior to their appointment with the GP. It is inherent in the nature of brief opportunistic advice that patients cannot be given warning of this or it ceases to be opportunistic.

We will ask to keep anthropometric and demographic data of patients who decline to participate in the trial. The researcher will record evidence of verbal consent for this on the Trial Screening Form.

#### Participant recruitment rate

We anticipate nine adults will consult per GP per session, of whom at least 25% will be obese and 75% of these will agree to participate in the study. In reality, the population of consulters is likely to be biased towards people with obesity because of its association with chronic disease, so the 25% is likely to be an underestimate. In trials of brief intervention for smoking cessation, recruitment rates (where they could be assessed) were high (100% [32], 93% [33], 88% [34], 89% [35], 87% [36], 96% [37], 92% [38], 90% [39]). As nearly all patients who are obese believe they have a weight problem and 84% would welcome GP support to manage this [25], we believe that 75% uptake is achievable. These figures would require us to attend 1,054 sessions and, with the staffing available, this could be achieved in 46 weeks to obtain the sample size of 1,824. Each GP will have intervened for about six sessions, which appears reasonable. The approach outlined here with the RA ‘in the waiting room’ was the most common approach used in other trials of brief interventions.

